### Objectives {7}

The primary objective of this study is to investigate if a single high dose of vitamin D, in addition to treatment as usual (TAU), reduces the length of the hospital stay in patients with COVID-19 and vitamin D deficiency. Furthermore, we have defined the following parameters as secondary outcomes: the necessity of ICU treatment, overall mortality, percentage of patients with 25-hydroxyvitamin D > 50 nmol/L (> 20 ng/mL) at day 7, changes in serum calcium, phosphorus, 25-hydroxyvitamin D, parathyroid hormone (PTH), and the development of sepsis. We hypothesized that time to recovery is shorter in the single high-dose vitamin D group relative to the standard treatment group.

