### Eligibility criteria {10}

Participants are eligible to participate in the study after giving written, informed consent when hospitalized on a general medicine ward due to ongoing, PCR-confirmed SARS-CoV-2 infection, aged ≥18 years with laboratory-confirmed vitamin D deficiency defined as a serum 25-hydroxyvitamin D concentration ≤ 50 nmol/L (≤20 ng/mL). Patients will be included independently of the severity of the disease.

The presence of any of the following conditions will lead to the exclusion of the participant: known hypersensitivity to one of the vitamin D products used in this study or to one of the adjuvants in the drug’s composition, active malignancy, hypercalcemia, granulomatous diseases such as sarcoidosis, history of renal stones within the past year, pregnancy/breastfeeding, previous enrolment into the current project, or another interventional trial.

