**Table Tabb:** 

ICU stay	Yes/no
	If yes, length of the ICU stays (admission to discharge)
	Requirement for mechanical ventilation
Overall mortality	
Vitamin D serum concentration	% of patients with 25-(OH)D > 50 nmol/L at day 7
	25-(OH)D
Laboratory parameters	Calcium
	Phosphorus
	Parathyroid hormone (PTH)
Sepsis	% of patients who develop a sepsis
Complications	Complications during the hospitalization due to COVID-19
Vital signs	Blood pressure (BP)
	Heart rate (HR)
	Respiratory rate (RR)
	Blood oxygen saturation
	Need of oxygen and how much
Quality of life (SF-12 Questionnaire)	At baseline, 28 days, and 3 months after inclusion

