### Participant timeline {13}

### Sample size {14}

To calculate the sample size, we looked at an interventional study of vitamin D, which examined the length of hospital stay as an outcome and what is known about the median length of hospital stay in patients hospitalized with COVID-19. A randomized, double-blind, placebo-controlled trial examined the effects of adjunctive vitamin D in adults hospitalized with community-acquired pneumonia (CAP) on time to recovery [28]. The primary outcome was the complete resolution of chest radiograph infiltrates at 6 weeks post-study treatment. Secondary outcomes included length of hospital stay, intensive care admission, and return to regular activity. At the same time, adjunctive vitamin D did not affect the primary outcome (*OR* 0.78, 95% *CI* 0.31 to 1.86, *p* = 0.548). There was evidence it increased the complete resolution of pneumonia in participants with baseline vitamin D levels < 25 nmol/L (*OR* 17.0, 95% *CI* 1.40–549.45, *p* = 0.043). Although not significant, the results indicated that patients in the intervention group had shorter length of hospital stay (mean = 3.8, *SD* = ± 3.1, *n* = 60) when compared with patients in the placebo group (mean = 4.8, *SD* = ± 6.5, *n* = 57), which indicates a small effect size (Cohen’s *d*) of 0.1980. The study indicated a 20% reduction in length of hospital stay.

Considering the above results in the light of COVID-19, more extended hospital stays in COVID-19 patients are expected. In smaller observational studies describing the clinical course of hospitalized COVID-19 patients in China, a median hospital stay of 12 days (*IQR* 9–15) (*n* = 137) [1] or of 10 days (*IQR*, 7.0–14.0) among those discharged alive (*n* = 47) [29] were observed. Guan et al. presented the clinical characteristics of 1099 patients with laboratory-confirmed COVID-19, and the median length of hospital stay was reported to be 12 days (*IQR* = 10–14) [30], which we will take as a basis for our sample size calculation.

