Sample size calculation was performed using the function “power.t.test” from the R package “stats” with the following parameters [31]: alpha = 0.05, power = 0.80, sigma = 2.96, delta (difference in the primary outcome between intervention and control group) = 2, and alternative hypothesis = two-sided, which resulted in a minimum of 35 patients per group, therefore a total of 70 patients. With a conservatively estimated 10% dropout rate, including the loss to follow-up, and a block size randomization of four, we decided to include 80 patients.

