### Statistical methods

#### Statistical methods for primary and secondary outcomes {20a}

A statistical analysis plan documented detailed methodology for summaries and statistical analyses of the data collected in this trial. The statistical analysis plan is finalized analysis [31]. We will summarize our results using descriptive statistics.

The primary analysis comparing the mean length of hospital stay between the two groups will be performed on the dataset of all randomized patients for whom the outcome measure is available. A two-sided independent Student’s *t*-test will be used following log-normal transformation as Feng et al. [32] suggested. The time to discharge will be assessed up to 3 months, with failure to reach discharge or die before that day considered as right censored at 3 months. Patients who are admitted to ICU or change wards within the hospital can continue the study and their data can be analyzed as planned, since the intervention can be continued, and daily visit data are available within the electronic patient documentation system. For patients who are transferred to another hospital, the primary endpoint will be taken from the respective discharge letter, which is by standard sent from the following hospital to the referring hospital. If this data is not available, the patient will be considered as right censored at the date of transfer.

In the secondary outcome analyses, mean levels of calcium, phosphorus, 25-hydroxyvitamin D, 1,25-dihydroxy vitamin D, and PTH will be compared using two-sided independent Student’s *t*-tests. To compare the proportion of patients who died, were admitted to ICU, developed sepsis, and as the proportion of patients with 25-hydroxyvitamin D ≥ 30 ng/mL at discharge between the two groups, either the χ ^2^ test or the Fisher exact probability test will be used. The Fisher exact probability test is an excellent non-parametric technique for comparing proportions when the two independent samples are small.

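### The vitamin D responder outcome is declared as above 50 nmol/L at day 7, but the statistical methods test at least 30 ng/mL (75 nmol/L) at discharge

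*Protocol article*

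**What the plan says.** The outcome is declared in three places in the protocol article, always in the same way:

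- Objectives {7}: "percentage of patients with 25-hydroxyvitamin D > 50 nmol/L (> 20 ng/mL) at day 7".
- Outcomes {12}, table: the percentage "of patients with 25-(OH)D > 50 nmol/L at day 7".
- Plans for assessment and collection of outcomes {18a}, table: the same entry again.

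The analysis is stated once, in the statistical methods section {20a}. For deaths, ICU admissions, sepsis and the vitamin D responder proportion, the χ² "test or the Fisher exact probability test will be used". The responder proportion named there is patients with 25-hydroxyvitamin D at or above "30 ng/mL at discharge between the two groups".

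The same paragraph of {20a} compares mean 1,25-dihydroxy vitamin D between groups. That analyte is not in the Objectives or in either outcome table.

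The eligibility criteria {10} require a "serum 25-hydroxyvitamin D concentration ≤ 50 nmol/L (≤20 ng/mL"), so every participant enters at or below the declared cut-off.

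**The concern.** A secondary outcome should be analysed as it is declared. Here an analyst who follows {20a} literally would report a proportion that no outcome list contains, and would have no named test for the one that is listed. Within the article two definitions are live, and nothing in it says which takes precedence.

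The time point is a second difficulty. The primary outcome is time from enrolment to discharge, and the trial is built to find that the high dose shortens it. A responder status read at discharge is thus read at a moment that treatment is meant to move. If the primary hypothesis is true, treated patients are sampled sooner after the dose than controls. A fixed day 7 does not have this feature.

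**Working it through.** **The plan's own figures.** The article states no sample size or power for the responder outcome, so there is none to reproduce. The primary calculation uses "alpha = 0.05, power = 0.80, sigma = 2.96" and a "difference in the primary outcome between intervention and control group) = 2" days. The normal approximation returns the stated 35 per group; the exact t-test gives 35.37, with power 0.796 at 35. Only the 2-day difference is carried forward.

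**Are the two thresholds the same value in different units?** The Objectives and the eligibility criteria both equate 50 nmol/L with 20 ng/mL.

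- Factor: 50 / 20 = 2.5 nmol/L per ng/mL.
- 30 ng/mL × 2.5 = 75 nmol/L.
- 75 / 50 = 1.5.

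They are different thresholds.

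**Side by side.**

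| Feature | Objectives and both outcome tables | Statistical methods {20a} |
|---|---|---|
| Threshold | 50 nmol/L (20 ng/mL) | 30 ng/mL (75 nmol/L) |
| Inequality | strictly above | at or above |
| Time | day 7 | discharge |
| Test named in the article | none | χ² or Fisher |

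**Are the two time points nearly the same?** For the series that the sample size section adopts, "the median length of hospital stay was reported to be 12 days", with an IQR of 10 to 14. If stay is taken as normal with mean 12 and SD 2.96, the share discharged by day 7 is Φ((7 − 12)/2.96) = 4.6%. With mean 10 (12 minus the design difference of 2) it is Φ((7 − 10)/2.96) = 15.5%. For most patients day 7 and discharge are different days. At the design effect, discharge samples fall about 12 − 10 = 2 days apart between arms.

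**Can the threshold change the result?** The article gives no expected 25-(OH)D distribution, so this is an illustration on assumed values: normal 25-(OH)D, means 60 and 40 nmol/L, SD 20, 40 per arm, two-sided alpha 0.05. The power formula is Φ[(d − 1.96·se0)/se1], where d is the difference in proportions, se0 the pooled and se1 the unpooled standard error.

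- Cut-off 50: responders 1 − Φ(−0.5) = 69.1% against 1 − Φ(0.5) = 30.9%. Power = Φ[(0.383 − 1.96 × 0.1118)/0.1033] = 0.94.
- Cut-off 75: responders 1 − Φ(0.75) = 22.7% against 1 − Φ(1.75) = 4.0%. Power = Φ[(0.187 − 1.96 × 0.0760)/0.0731] = 0.70.

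With means 75 and 45 and the same SD, power is above 0.99 at both cut-offs. The choice can matter, but need not.

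**How many day-7 values would early discharge remove?** This bears on the fix, not on the contradiction. A log-normal with median 12 and IQR 10 to 14 has log-scale SD ln(14/10)/1.349 = 0.249. Scaling the treated median by 10/12 gives:

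- stay of 7 days or less: 1.5% of controls, 7.6% of treated;
- stay of 6 days or less, so that a patient leaving on day 7 can still be sampled: 0.3% and 2.0%.

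**The case against.** **The unseen SAP.** Section {20a} refers to a finalised statistical analysis plan, which is not at hand and may use the declared definition. A reader might infer that the declared outcome will never be tested, or that the choice is open once data are seen. The article supports neither. It shows only that no test is named in it for the day-7 proportion, and it keeps the analysing statistician blinded. What remains is that {20a} does not leave the definition to the SAP: it states a different one.

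**Confounding.** A reader might also infer that the discharge comparison is confounded by length of stay. That goes too far. The comparison is still between randomised arms, and the article contains no 25-(OH)D kinetics from which to say how far a gap of about 2 days would move the proportion. The supportable statement is that sampling time would depend on treatment if treatment works, which makes the result harder to interpret.

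**Day 7 loses patients too.** Wider or earlier stay distributions cited in the sample size section would raise the share discharged by day 7, to 24.4% of controls and 36.7% of treated for the series with median 10 and IQR 7 to 14. But the design does not rest on that 47-patient series of people discharged alive, and the figures describe missingness in the declared outcome, not the conflict between definitions. On the adopted IQR the loss is small.

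**Intent.** The tables list 25-(OH)D without a time point, so a discharge measurement is not in itself outside the declared data. The article also does not say outright which responder definition was meant. Three concordant statements against one, and an entry limit equal to the declared cut-off, favour day 7 but do not prove it.

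**Importance.** This is one biochemical secondary outcome. That stands, and it limits the severity.

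**Conclusion.** The contradiction is real and internal to the current text. Units do not explain it, and no redaction or amendment history is involved. The analysed cut-off is 1.5 times the declared one, the inequality differs, and a fixed day is replaced by a treatment-dependent time that would differ by about 2 days between arms at the design effect. The threshold and inequality conflict rest on no assumption beyond the article's own unit equivalence. The 2-day gap assumes that the design difference holds and that the dose is given close to enrolment. The power figures are illustrative only.

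The naming of 1,25-dihydroxy vitamin D is a smaller mismatch of the same kind: it is analysed but is in no visible outcome list. The participant timeline is not legible in the available text, so whether it was scheduled cannot be checked.

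The primary outcome, its analysis and the sample size are untouched. Severity: should-fix.

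**What to change.** Before unblinding:

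1. In section {20a}, replace the responder proportion with the declared one, 25-(OH)D above 50 nmol/L (20 ng/mL) at day 7, and assign the χ² or Fisher test to it. This is the definition stated three times, and it means that the deficiency defined at entry has been corrected. Make the same change in the SAP if it carries the {20a} wording.
2. Label the proportion at or above 30 ng/mL at discharge as exploratory, or remove it. Do the same for 1,25-dihydroxy vitamin D.
3. For day-7 values missing because of early discharge, apply the approach already in the missing-data section {20c}: retrieval from records, then multiple imputation by chained equations unless a stated reason to ignore the missing values applies. Do not substitute the last in-hospital sample, which would bring back a treatment-dependent sampling time in exactly those patients.

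The cost is a text correction in the statistical section and possibly the SAP. Section {20c} already requires that changes to the statistical plan be reported to the ethics committee. No new data and no change in sample size are needed.

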#### Interim analyses {21b}

Due to the relatively small sample size and short study duration, we will not identify stopping criteria nor perform interim analyses.

#### Methods for additional analyses (e.g., subgroup analyses) {20b}

To evaluate the safety of short-term vitamin D administration in the above-described population, linear/logistic mixed-effect models will be used to estimate treatment effects on safety parameters such as adverse events/laboratory parameters (e.g., serum calcium or PTH) and vital signs. If data permits, subgroup analyses will be performed, such as analyses stratified by gender or baseline vitamin D levels.

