A randomized placebo-controlled trial of high-dose vitamin D in critically ill adult patients with vitamin D deficiency found a significant in-hospital mortality reduction among patients with severe vitamin D deficiency compared to placebo [21]. In a further study of vitamin D status in patients with ARDS, Park and colleagues retrospectively examined data from 108 patients with ARDS for whom a vitamin D status was available; they observed that over 95% of these patients had vitamin D deficiency [22]. When examined according to quartile of serum 25-hydroxyvitamin D, a consistent inverse relationship between serum 25-hydroxyvitamin D and length of hospital and ICU stay among survivors was observed [22].

A treatment with vitamin D showed a significant reduction of inflammatory markers, a shorter time to recovery for patients with cough, gustatory sensory loss in patients with COVID-19, and vitamin D deficiency, without the occurrence of side effects [23, 24]. The anticipated risk of side effects due to a single high dose of vitamin D in this study is minimal, compared to the potential impact on preventing more extended hospital stays and worse outcomes in COVID-19. A single high dose of vitamin D in addition to smaller daily doses is secure and can be added to the current treatment guidelines for COVID-19 [23]. Vitamin D supplementation is a safe and cost-effective intervention, with multiple health benefits for patients with COVID-19 and vitamin D deficiency [25].

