### Assignment of interventions: allocation

#### Sequence generation {16a}

Participants will be randomly assigned to either the intervention or the control group in a 1:1 ratio. A statistician not involved in the data analysis generates a randomization list with study group allocation using R [31]. Randomization is carried out stratified by center using block randomization with a block size of four to account for differences in standard of care. The randomization master list will be handed over to the university hospital pharmacy in Basel, where the study drug will be labeled and packaged accordingly. In case of an adverse event (AE) or serious adverse event (SAE) that requires an emergency code break, the hospital pharmacy can decode the randomization immediately.

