#### Adverse event reporting and harms {22}

##### Reporting of SAEs

An adverse event (AE) is defined as any untoward medical occurrence in a patient, or a clinical investigation participant administered a pharmaceutical product, which does not necessarily have a causal relationship with the study procedure. An AE can be any unfavorable and unintended sign (including an abnormal laboratory finding), symptom, or disease, whether or not related to the medicinal (investigational) product. A serious adverse event (SAE) is classified as any untoward medical occurrence that results in death, is life-threatening, requires in-patient hospitalization or prolongs existing hospitalization, results in persistent or significant disability/incapacity, or is a congenital anomaly/congenital disability.

In addition, critical medical events that may not be immediately life-threatening, result in death, or require hospitalization but may jeopardize the patient or require intervention to prevent one of the other outcomes listed above should also usually be considered serious.

All SAEs must be reported immediately and within a maximum of 24 h to the sponsor-investigator of the study. The sponsor-investigator will re-evaluate the SAE and return the form to the site. SAEs resulting in death are reported to the ethics committee via BASEC within 7 days.

All involved ethics committees receive SAEs resulting in death in Switzerland via sponsor-investigator via BASEC within 7 days.

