## Discussion

The primary aim of this study is to determine whether a high dose of vitamin D improves the course of COVID-19 or not. Two issues might affect the ability to recruit patients for this trial: first levels of vitamin D are the highest by the end of summer [35], which could lead to problems in recruiting. After the full ethics approval and the approval from Swissmedic, the recruitment period is expected to start at end of 2020 or early 2021. Shorter days and less exposure to sunlight most certainly lead to a decreasing serum concentration of vitamin D. Therefore, we anticipate that we will not have recruiting problems due to high vitamin D levels.

Secondly, travel regulation and other policies can change day by day and are carefully monitored by the Swiss government, which leads to a more unpredictable situation for this and other studies investigating COVID-19.

While the number of patients hospitalized with COVID-19 declined between April and August, numbers have started to rise again. Latest studies have shown a link between international and domestic air travel and the number of COVID-19 cases, so unless air travel is restricted again, we can expect an increasing number of cases [36, 37]. The same can be applied for lockdown policies and other public health measures, leading to decreasing cases [38, 39] and subsequent rebounds after gradually releasing the measures.

There are minimal risks in the participation in this study. Almost no side effects are reported when using a high vitamin D dosage, but it has a potential short and may also long-term benefit [23, 24, 40]. Some recent findings indicate an association between vitamin D deficiency and disease severity [23, 41, 42]. However, there is a lack of consensus on the dosage of vitamin D supplementation [40]. With this trial, we hope to make a valuable contribution in clarifying the role of vitamin D in COVID-19 and its effect on short-term outcomes. The crucial point is that vitamin D supplementation is a simple, safe, and inexpensive possibility to correct vitamin D deficiency, with potential benefits to patients with COVID-19 [43]. On a larger scale, the benefit that effective treatment of vitamin D deficiency in patients with COVID-19 could have on the overall costs of the health care system must also be considered. The authors hope to make a valuable contribution to future treatment guidelines for patients with COVID-19.

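### For rare specific adverse events, the logistic mixed-effect model named for safety is poorly suited to 40 patients per arm: if all events fall in one arm it gives no finite odds ratio and no reliable test

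*Protocol article*

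**What the plan says.** The section on additional analyses {20b} names the method for safety: "linear/logistic mixed-effect models will be used to estimate treatment effects on safety parameters such as adverse events/laboratory parameters", with vital signs modelled the same way. It is the only between-arm method that the article gives for adverse events.

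The sample size section {14} says "we decided to include 80 patients", and sequence generation {16a} says "Participants will be randomly assigned to either the intervention or the control group in a 1:1 ratio", so the plan is for 40 per arm.

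On expected harm, the background {6a} says "The anticipated risk of side effects due to a single high dose of vitamin D in this study is minimal" and the Discussion says "Almost no side effects are reported when using a high vitamin D dosage". Both statements concern side effects of vitamin D. Adverse events are defined much more widely under Reporting of SAEs: "An adverse event (AE) is defined as any untoward medical occurrence in a patient", "whether or not related to the medicinal (investigational) product".

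For death, ICU admission, sepsis and a 25-hydroxyvitamin D threshold, the main statistical methods section {20a} uses a chi-square or Fisher test and remarks that the "Fisher exact probability test is an excellent non-parametric technique for comparing proportions when the two independent samples are small". It does not extend this to adverse events.

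**The concern.** A logistic model estimates a treatment effect only if both arms contain patients with and without the event. If one arm has none, the likelihood keeps rising as the log-odds ratio grows, and no finite maximum exists (separation). A random centre effect does not cure this. Nor does a random patient effect with repeated records, as long as one arm has no event at all.

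The harms most informative about the study drug are specific and probably rare, so this pattern is plausible for them. It is also the pattern that a real harm of the high dose would produce. The stated model would then give an unusable estimate, and its p-value would depend on which test the software prints. The article plans no interim analysis, so the final comparison carries the between-arm safety evidence.

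**Working it through.** **Inputs.** 80 patients, 1:1, hence 40 per arm (36 per arm after the article's 10% dropout: 80 × 0.9 = 72). The article states no event rate, so rates from 0.5% to 20% are assumed.

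**The plan's own figure.** The only size calculation is for length of stay (difference 2, SD 2.96, two-sided 0.05, power 0.80). The normal approximation gives 2 × (1.96 + 0.84)² × (2.96/2)² ≈ 34.4, so 35 per group as stated; the exact t-based solution is 35.37. Then 70/0.9 = 77.8, rounded up to 78, and the next multiple of the block size four is 80. So 40 per arm is a sound basis. There is no safety figure to reproduce.

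**Step 1: the estimate.** With k events of 40 against 0 of 40, the log-odds ratio is log[k/(40 − k)] − log[0/40], which is infinite. Fits with the treatment term alone, by iteratively reweighted least squares, stop at an arbitrary point. For 6 v 0 one stopping rule gives 18.8 with SE about 2,800, another 21.8 with SE about 12,600. The Firth estimate adds 0.5 to each cell and stays finite: for 6 v 0, (6.5/34.5)/(0.5/40.5) = 15.3.

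| Events | Wald p | Likelihood-ratio p | Fisher p | Firth OR |
|---|---|---|---|---|
| 3 v 0 | 0.995 | 0.039 | 0.24 | 7.6 |
| 5 v 0 | 0.995 | 0.007 | 0.055 | 12.5 |
| 6 v 0 | 0.995 | 0.003 | 0.026 | 15.3 |
| 8 v 0 | 0.995 | 0.0005 | 0.005 | 21.2 |

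With 36 per arm the picture is the same (6 v 0: Wald 0.995, Fisher 0.025).

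**Step 2: is the likelihood-ratio test a rescue?** Given three events in total and no true effect, the chance that all three fall in one arm is 2 × C(40,3)/C(80,3) = 2 × 9,880/82,160 = 0.24. The likelihood-ratio test calls each such split significant at 0.05. Fisher's conservatism does not explain the gap: counting the observed split at half weight (mid-p) gives 0.24/2 = 0.12 at 3 v 0 and 0.026/2 = 0.013 at 6 v 0, still well above 0.039 and 0.003.

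**Step 3: how often is exactly one arm empty?** With equal risk r in both arms and q = (1 − r)^40, the probability is 2q(1 − q):

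| Assumed risk | 0.5% | 1% | 2% | 5% | 10% | 20% |
|---|---|---|---|---|---|---|
| Exactly one empty arm | 0.30 | 0.44 | 0.49 | 0.22 | 0.03 | 0.0003 |

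For a real harm, take a 15% risk in the high-dose arm. The chance of no control events and at least six treated events is 0.38 at a 1% control risk, 0.25 at 2%, 0.07 at 5% and 0.008 at 10%.

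**Step 4: what simpler summaries would show.** For 6/40 v 0/40 the risk difference is 15 points, with a Newcombe 95% interval of 3 to 29 points. For 0/40 the exact upper 95% limit is 1 − 0.025^(1/40) = 8.8%. Both are finite and readable where the model estimate is not.

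**The case against.** A reader might infer that the plan expects almost no adverse events, so that the safety analysis as a whole will break down and report no difference in the face of real harm. The article does not support this, for three reasons.

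- The low expectation is for side effects of vitamin D. Adverse events as defined include those of the illness, in inpatients with COVID-19 of any severity. For a frequent composite such as any adverse event, an empty arm is improbable (3% at a 10% risk).
- A finding of no difference requires a Wald test, and the article names no test. The likelihood-ratio test from the same model gives 0.003 at 6 v 0. A standard error in the thousands is also a visible fitting failure that an analyst may well notice.
- Harm detection does not rest on this model alone. Death, ICU admission and sepsis have their own tests, calcium is compared as a mean, descriptive statistics are planned, and serious events and safety signals have reporting routes.

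All three stand and limit the point to rare specific events. Two further objections stand in part. Fisher's test is itself non-significant up to 5 v 0, so it changes the 0.05 verdict against Wald only from 6 v 0; but it is valid at every count, and the likelihood-ratio test is not. And a separate statistical analysis plan, not shown, may hold a sparse-data rule. The absence of such a rule from the article is therefore no fault. What remains is that the article states a method that suits rare events poorly, while commending a better one for small samples in the preceding statistical section.

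**Conclusion.** The point holds for rare specific adverse events and is minor. With about 40 per arm and every event of a type in one arm, the named model yields no finite odds ratio, its Wald test is uninformative, and its likelihood-ratio test overstates the evidence. This pattern is common if the risk is roughly 0.5% to 5% (probability 0.22 to 0.49) and largely disappears from 10% upward.

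The conclusion rests on assumed event risks, equal in the two arms for those probabilities, and on fits without a random effect, which would not make the treatment estimate finite. It concerns an additional safety analysis and touches neither the primary result nor the sample size.

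**What to change.** In section {20b}, separate binary adverse events from repeated measurements. For each binary type, report the number of patients with at least one event per arm, the risk difference with a score-type 95% CI (and the exact upper limit when an arm has none), and Fisher's exact test. If an adjusted odds ratio is wanted, use Firth-penalised logistic regression. Keep the linear mixed models for repeated laboratory values and vital signs.

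This takes a sentence or two and no new data. The small downside is that Fisher's test is conservative and does not adjust for centre, the stratification factor.
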